## Abstract

**Introduction:**

Cancer, malnutrition, and surgery negatively impact patient’s immune system. Despite standardized surgical technique and the development of new perioperative care protocols, morbidity after cystectomy remains a serious challenge for urologists. Most common postoperative complications, such as infections and ileus, often lead to longer length of stay and worse survival. The immune system and its interaction with the gut microbiota play a pivotal role in cancer immunosurveillance and in patient’s response to surgical stress. Malnutrition has been identified as an independent and modifiable risk factor for both mortality and morbidity. Immunonutrition (IN) may improve the nutritional status, immunological function, and clinical outcome of surgical patients. Aims of the study are (1) to evaluate the impact of IN on morbidity and mortality at 30 and 90 days after cystectomy and (2) to determine immune and microbiota signature that would predict IN effect.

**Methods:**

This is a randomized, multicentric, controlled, pragmatic, parallel-group comparative study, supported by the Swiss National Science Foundation. A total of 232 patients is planned to be enrolled between April 2023 and June 2026. Three participating centers (Lausanne, Bern, and Riviera-Chablais) have been selected. All patients undergoing elective radical and simple cystectomy will be randomly assigned to receive 7 days of preoperative IN (Oral Impact^®^, Nestlé, Switzerland) versus standard of care (control group) and followed for 90 days after surgery. For the exploratory outcomes, blood, serum, urine, and stool samples will be collected in patients treated at Lausanne. In order to determine the impact of IN on immune fitness, patients enrolled at Lausanne will be vaccinated against influenza and the establishment of the vaccine-specific immune response will be followed. Analysis of the microbiota and expression of argininosuccinate synthetase 1 as potential biomarker will also be performed.

**Discussion and conclusion:**

Strengths of the INCyst study include the randomized, multicenter, prospective design, the large number of patients studied, and the translational investigation. This study will challenge the added value of preoperative IN in patients undergoing cystectomy, assessing the clinical effect of IN on the onset of postoperative morbidity and mortality after cystectomy. Furthermore, it will provide invaluable data on the host immune response and microbiota composition.

**Trial registration:**

ClinicalTrials.gov NCT05726786. Registered on March 9, 2023.

**Supplementary Information:**

The online version contains supplementary material available at 10.1186/s13063-024-08536-5.

## Introduction

Radical cystectomy (RC) with extended bilateral pelvic lymph node dissection (PLND) represents the best available treatment for muscle-invasive BC [1]. Furthermore, this major surgery may be the treatment of choice for non-malignant pathologies, such as interstitial cystitis, painful bladder syndrome, neurogenic bladder, hemorrhagic radiation cystitis, infectious diseases of the bladder, endometriosis, and refractory genitourinary fistulae [2] in patients who have failed previous conservative therapy.

Although cystectomy is considered as an extended major surgery, it has unique features that preclude any outcomes extrapolation from other abdominal surgeries (i.e., colonic resections, gynecologic procedures). These include lymph node resection, longer operative time, significant bleeding, urinary diversion with bowel resulting in metabolic changes, and peritoneal soiling with urine [3].

Despite standardized surgical technique and the development of new perioperative care protocols, cystectomy morbidity remains a serious challenge for urologists. Postoperative complications lead to longer length of stay and worse survival. Infectious complications, including pneumonia, urinary tract infections, surgical site infections, septicemia, and shock, are relatively frequent after cystectomy, rated between 25 and 45% [4, 5]. Patients undergoing cystectomy for a bladder cancer or a benign disease have the similar risk of complications [6]. Antibiotic prophylaxis practices are highly heterogeneous in cystectomy and there is a lack of adherence in guidelines [7].

Careful perioperative risk reduction in patients undergoing major surgery is an evolving key concept to decrease postoperative morbidity rates. Many risk factors, such as repeated radio-chemotherapy regimens, pre-existing co-morbidities, and increased age, can hardly be influenced. Although malnutrition has been identified as an independent risk factor for morbidity and mortality after cystectomy [8–10], there is no recommendation with regard to preoperative screening and/or treatment of malnutrition in guidelines for cystectomy. In most of hospitals where cystectomies are performed, there is no standardized malnutrition screening policy and malnourished patients undergoing surgery are therefore neither identified nor treated.

Another major pathogenic factor leading to postoperative morbidity is the so-called surgical stress response. Nowadays, it has been clarified that surgery induces a complex cascade resulting in inflammatory response, immune suppression, and altered metabolism with hypercatabolism, which altogether lead to impaired wound healing and multi-organ failure. The mediators of this endocrine-metabolic stress response are cytokines, arachidonic acid, nitric oxide, and free oxygen radicals. While the mechanisms mentioned above have been extensively studied, to date, no single intervention has been shown to eliminate postoperative morbidity and mortality. Consequently, immunosurveillance and therefore successful cancer treatment relies on maintaining an unharmed immune system.

Immunonutrition (IN) aims to improve the nutritional status, immunological function, and clinical outcome of cancer patients. When applied to cancer patients treated by radiation or chemotherapy (i.e., not undergoing surgery, thus avoiding surgical stress response), IN has been shown to increase T lymphocyte counts and to decrease inflammatory and oxidative stress response [11]. Many randomized controlled trials and meta-analyses have demonstrated that IN allows for a reduction of complication rate, infections, and length of stay after major abdominal surgery [12]. Unfortunately, very few data are available on the impact of IN on infectious complications after cystectomy [13, 14].

The aims of this study are (1) to evaluate the impact of IN on morbidity and mortality at 30 and 90 days after cystectomy and (2) to determine immune and microbiota signature that would predict IN effect.

## Methods

### Study design

The present study (approval #2022–01528 version 5) is designed as a multicenter, prospective, controlled, pragmatic, superiority, parallel-group comparative clinical trial with block randomization stratified by centers (Fig. 1 and Table 1). Patients will be randomly assigned to 2 groups (per center randomization): intervention group (7 days of preoperative oral supplementation with an immune-enhanced oral nutrition (Oral Impact®, Nestlé Nutrition, Switzerland)) or control group (standard of care, no preoperative IN). During an overall study duration of 4 years, a total of 232 patients (116 in each arm) will be included (Table 2
). Allocation consignment will be generated by a dedicated research nurse at each center, through centralized block randomization via the Interface Web Response System (IWRS) developed within the electronic case report form (eCRF). Equilibrated randomization will be performed on a site-stratified basis to avoid imbalanced randomization between clinical sites where patient recruitment may differ. The allocation sequence is concealed from the investigators enrolling and assessing the patients.

**Fig. 1 Fig1:**
[figure not shown]
Inclusion and exclusion criteria of the INCyst Trial

**Table 1 Tab1:** Trial registration data set according to World Health Organization

Data category	Information
Primary registry and trial identifying number	ClinicalTrials.gov NCT05726786
Date of registration in primary registry	March 9, 2023
Secondary identifying numbers	2022–01528 (Swissethics); SNCTP000005406 (KOFAM)
Source(s) of monetary or material support	Swiss National Science Foundation
Primary sponsor	University Hospital of Lausanne (CHUV)
Secondary sponsor(s)	None
Contact for public queries	[name]. [name] ([contact])
Contact for scientific queries	[name]. [name] ([contact])
Public title	The impact of immunonutrition on postoperative complications in patients undergoing bladder removal surgery
Scientific title	The role of preoperative immunonutrition on morbidity and immune response after cystectomy: protocol of a multicenter randomized controlled trial (INCyst Trial)
Countries of recruitment	Switzerland
Health condition(s) or problem(s) studied	Determination of infectious complications rate at 30 days after surgery
Intervention(s)	Drug: Oral Impact^®^, Nestlé Health Science, Switzerland
Key inclusion and exclusion criteria	Inclusion criteria: age ≥ 18 years, patient undergoing open cystectomy (for all reasons) Exclusion criteria: contraindications to immunonutrition (e.g., known hypersensitivity or allergy to lactose, fish oil, or soy lecithin), severe diarrhea requiring medical attention, current treatment with any immunosuppressive drug
Study type	Multicenter, prospective, controlled, pragmatic, parallel-group comparative study with block randomization stratified by centers
Date of first enrolment	April 2023
Target sample size	232
Recruitment status	Recruiting
Primary outcome(s)	Determination of the Comprehensive Complication Index (CCI) at 30 and 90 days after surgery Determination of the mortality rate at 30 and 90 days after surgery Determination of the postoperative complication-free survival
Key secondary outcome	Identification of biomarkers predictive of postoperative complications studying the patient’s immune and microbiome signature

Nutritional Risk Status (NRS) Score will be performed in each patient before inclusion. Preoperative carbohydrate loading will be allowed in both groups in case of malnutrition and at discretion of the referent physician. Malnutrition status will not impact the group allocation. This trial will be conducted in accordance with the Good Clinical Practice Guidelines and applicable local regulations. Moreover, we used the SPIRIT reporting guidelines to write the protocol (Supplementary Table 1). The INCyst Trial is supported by the Swiss National Science Foundation (#32003B_207837). The Swiss National Science Foundation is not involved in the design of the study and collection, analysis, and interpretation of data and in writing the manuscript.

**Table 2 Tab2:** Schedule of enrolment, interventions, and assessments

**Study periods**	**Screening**	**Pre-operative**	**Follow-up**				
**Visit**	**V0**	**V1**	**V2**	**V3**	**V4**	**V5**	**V6**
Time (day)	J-30* /-8	J-1/0	J0+1	J0+5	end of hospitalization	J0+30+/-10	J0+90 +/-20
Informed consent	X						
Demographic characteristics	X						
Medical history	X						
In-/Exclusion criteria	X						
Physical examination	X	X	X	X	X	X	X
Weight		X	X	X	X	X	X
**Laboratory samples (only Lausanne)**							
Blood (50ml/sample)	X	X				X	
Urine (5 to 300 ml/sample)	X	X				X	
Stools	X	X				X	
Arginine level	X	X					
Tissue (ASS1 expression analysis)		X					
Fresh Tissue (oncological patients)		X					
Influenza vaccination	X						
NRS	X						
Eligibility and Randomization	X						
Post-operative infectious complications						X	X
Comprehensive Complication Index (CCI)						X	X
EORTC-QLQ-C30 questionnaire	X					X	X
Peri-operative management					X		

### Clinical outcomes

The primary endpoint is to investigate the infectious complications rate at 30 days after surgery. All type of infectious complication will be considered and graded according to the Clavien’s grade.

Secondary clinical outcome is Comprehensive Complication Index (CCI) evaluated at 30 and 90 days after surgery. Postoperative complications will be graded according to their severity. A validated therapy-oriented, modified Clavien-Dindo classification will be used to asses complication grade [15]: major complications are defined as grade 3–4; grade 5 corresponds to mortality.

Mortality rate at 30 and 90 days after surgery, postoperative complication-free survival, treatment compliance, impact of IN on oncologic and non-oncologic patients, role of IN in patients undergoing neoadjuvant chemotherapy, and quality of life after surgery will also be investigated.

### Exploratory outcomes

For exploratory outcomes, blood, serum, urine, and stool samples will be collected in patients treated at the site of Lausanne. The main goal is to characterize different immune parameters to define a signature that will be predictive of the IN efficacy and that will guide to select patients likely to benefit from IN.

Percentages of different immune cell subsets from the peripheral blood mononuclear cells (PBMCs) will be measured by flow cytometry. We will study the frequency of different subsets of immune cells such as CD3^+^ T cells, regulatory CD4^+^ T cells, natural killer (NK) cells, and myeloid-derived suppressor cells. Furthermore, the expression of immune checkpoints (PD-1, TIM-3, BTLA, CTLA-4, and TIGIT) on T cells from blood will also be performed ex vivo.

To determine the influence of IN on immune response generated in vivo, T-cell specific immune response against influenza will be monitored in the PBMCs before vaccination and after. It is well known that the presence of polyfunctional T cells (i.e., capacity to produce several cytokines at the same time) may be beneficial to the outcome of a disease, especially in cancer [16–18]. Thus, T-cell polyfunctionality assessment may provide a surrogate for potential antitumor immune response. We will stimulate blood T cells from patients in vitro either with anti-CD3 and anti-CD28 antibodies or with a pool of peptides from influenza and measure the production of TNF-α, IFN-γ, IL-2, IL-4, IL-10, IL-17, and CD107a by flow cytometry. We also intend to determine the concentration of inflammatory and suppressive cytokines in serum and urine using the classical Luminex assay, as we did in a previous clinical trial [19].

Furthermore, it is well known now that a disruption of the symbiosis between the microbiota and the immune system, as a result of antibiotic usage or diet alteration, may lead to the development and/or exacerbation of different diseases [20], supporting the fact that IN may impact the gut microbiota. Microbiota diversity and abundance will be thus determined by genomic sequencing and bioinformatics analysis on patient feces. Finally, argininosuccinate synthetase 1 (ASS1) expression will be analyzed by immunohistochemistry in order to evaluate whether its expression may alter the IN efficacy.

Biological material will be appropriately stored in a restricted area only accessible to authorized personnel according to the regulation of the urology biobank of Lausanne University Hospital (https://www.chuv.ch/fr/urologie/uro-home/recherche/axes-de-recherche/biobanque-durologie). No publication or report of any kind will contain patient’s names or any identifying features of single patients. No on-line or written document or communication will refer to participant’s personal detail.

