### Choice of comparators and protocol adherence

Oral Impact^®^ (IN) is an immune-modulating nutritional supplement containing arginine, omega-3 polyunsaturated fatty acids, and ribonucleic acid. Arginine is a key amino acid involved in multiple cellular processes as well as in lymphocyte function and its deficiency results in impaired adaptive immune response. It plays an active role in wound healing, muscle repair (by protein translation), and thrombosis prevention. The present design raises the issue of supplementing patients that are not at nutritional risk with Oral Impact®, resulting in overnutrition with potentially deleterious clinical consequences. However, this hypothesis has not been confirmed by others [23] and the product’s brochure stipulates that the administration of Oral Impact® in the preoperative phase is also indicated in well-nourished patients [24]. Moreover, surgery induces arginine deficiency and many patients with normal preoperative arginine concentrations cannot endogenously satisfy the metabolic demand after surgery.

Patients will be randomly assigned to receive 7 days of preoperative IN, three times a day (Oral Impact^®^) or will not receive oral IN supplements. Carbohydrate loading and protein drinks will be allowed in both groups. In the interventional group, patient’s compliance to the allocated treatment will be recorded by asking the patient how many nutritional supplements she/he has ingested preoperatively (ranging from 0 to 21 bags). Compliant patients will be defined by having drunk at least 14 of the 21 allocated nutritional supplements. To objectively verify and validate these subjective data, serum arginine levels will be assessed at enrolment (between day − 30 and day − 8) and at preoperative admission after intake of the allocated nutrition (day − 1).

Potential effective crossover between intervention groups will be assessed and recorded. As usual with interventions requiring voluntary adherence to a protocol, there is a risk for some participants from the IN arm do not comply with the intervention. Moreover, a mirroring risk exists for participants from the control group to access IN independently of the study protocol, since the product is commercially available. Recording such protocol deviations is mandatory for processing to a second line per-protocol analysis. However, the risks of crossover are very low.

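### ASS1 is to be tested as a factor that alters IN efficacy, but its only scheduled tissue sample comes after the IN course, so the marker may itself be affected by treatment

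*Protocol article*

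**What the plan says.** The protocol article, Exploratory outcomes, gives the purpose of the ASS1 measurement: "argininosuccinate synthetase 1 (ASS1) expression will be analyzed by immunohistochemistry in order to evaluate whether its expression may alter the IN efficacy".

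Table 2 sets its timing. In the block of laboratory samples limited to Lausanne, the row that begins "Tissue (ASS1 expression analysis" has a single mark, in the V1 column, which the day row places at day -1/0. The same table puts randomisation at V0, between day -30 and day -8.

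The section Choice of comparators and protocol adherence describes the treatment given between those two visits: "Patients will be randomly assigned to receive 7 days of preoperative IN, three times a day". The control arm receives no IN. On content, "Oral Impact^®^ (IN) is an immune-modulating nutritional supplement containing arginine" among other components. The same section describes the second serum arginine sample, also a V1 sample, as taken "at preoperative admission after intake of the allocated nutrition".

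**The concern.** To ask whether a marker alters the efficacy of a treatment, one compares the treatment effect between patients with high and low values of the marker. Randomisation protects that comparison only if the marker is fixed before treatment. Patients with high ASS1 in the IN arm then have true counterparts with high ASS1 in the control arm.

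A marker measured after treatment loses that protection if treatment can move it. Patients with high ASS1 in the IN arm would then be a mixture of those who were high all along and those whom IN made high, compared with control patients who were all high without IN. The difference in infection rate within that group would mix the effect of IN with a difference in patient type. It could suggest that ASS1 modifies the effect of IN when it does not, or conceal a real modification.

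At stake is how an exploratory result is read. A statement that ASS1 alters IN efficacy invites use of ASS1 before treatment, whereas the scheduled value would have been obtained only after it.

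**Working it through.** The documents give no figure on this point to reproduce. The check is one of timing, followed by a short argument on what could go wrong.

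**1. Order of events**

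| Event | Day relative to surgery | Source |
|---|---|---|
| V0, with randomisation | -30 to -8 | Table 2 |
| IN course, one arm only | the 7 days before surgery, so about -7 to -1 | Choice of comparators and protocol adherence |
| V1, the only ASS1 tissue | -1/0 | Table 2 |

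Three servings a day for 7 days is 3 × 7 = 21, the maximum that the article records for compliance. If V1 falls at the start of day -1, six days are complete, or 3 × 6 = 18 of 21 servings. If it falls on day 0, the course is finished. Either way the tissue follows all or nearly all of the IN. The article treats V1 as a post-intake visit for serum arginine.

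The section on patient selection calls the inclusion visit V1 when it describes the questionnaire, whereas Table 2 marks the baseline questionnaire at V0. This does not alter the conclusion, because the day row of Table 2, not the label, fixes when the tissue is taken.

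**2. Count of ASS1 samples.** Before IN: 0. After IN: 1.

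**3. What a shift would do.** Let *q* be the share of patients with high ASS1 before treatment, and *s* the share of low-ASS1 patients whom IN moves to high by V1. Suppose nobody moves the other way.

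- High group at V1, control arm: *q*, all high from the start.
- High group at V1, IN arm: *q* + *s*(1 - *q*).
- Share of that IN-arm group who were low at the start: *s*(1 - *q*) / [*q* + *s*(1 - *q*)].

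With *s* = 0 the share is 0 and the V1 value stands in for baseline without harm. With *s* > 0 the share is positive and the two high groups differ in kind. The documents give neither *q* nor *s*, so no bias can be computed.

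**4. Number of patients concerned.** Stated accrual is 50, 25 and 10 per year at the three sites, a total of 85. The expected number at Lausanne is 232 × 50/85 = 136.5, so about 136, or roughly 68 per arm under equal, site-stratified allocation. This is a head count from projected accrual, not a measure of bias.

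**The case against.** The strongest reply is that the mechanism is not in the documents. They say that the supplement contains arginine and that serum arginine is measured before and after intake. They do not say that a week of oral supplementation changes ASS1 on immunohistochemistry. If it does not, V1 tissue represents baseline expression well enough and nothing is lost. This stands, and it is why the point is stated as a possibility. It does not remove the point, because the schedule alone cannot show that ASS1 is unaffected.

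A second reply is that the outcome is exploratory, confined to one site and described in the abstract only as a potential biomarker. That also stands, and it limits the weight of the point.

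A third is that earlier tissue may not exist. The documents do not say that any is stored, and patients with benign indications are enrolled too. The fix must therefore work without it.

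A reader might go further and infer that the immune and microbiota work has the same flaw. Its aim is to "define a signature that will be predictive of the IN efficacy and that will guide to select patients likely to benefit from IN", and samples are also taken after IN (V1) and around day 30 (V5). The documents do not support that inference. In Table 2 the rows that begin "Blood (50ml/sample" and "Urine (5 to 300 ml/sample", and the row for stool, all have a mark at V0, before IN. A baseline signature is therefore feasible. Nothing says that V1 or V5 values enter it. The later samples suit the article's stated interest in how IN affects the vaccine response and the gut microbiota. Which visit feeds an exploratory model is detail that an article may leave to the full protocol.

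**Conclusion.** The point holds for ASS1 and is of low severity. As scheduled, the proposed modifier is measured after randomisation and after a treatment that only one arm received. Subgroup or interaction results based on it can be read as effect modification only on the unstated assumption that IN leaves ASS1 expression unchanged. The documents neither support nor contradict that assumption, so they do not show that the ASS1 analysis will be biased, and no size can be given. The conclusion rests on the visit columns of Table 2 as extracted. The randomised comparison of infections at 30 days is not affected.

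**What to change.** In the exploratory analysis text:

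1. Compare V1 ASS1 expression between the arms before any modifier analysis, and report the difference with its confidence interval. A clear difference means that V1 values should not be used as a modifier. A small difference is reassuring only as far as its interval is narrow, and it does not prove that no patient's value moved.
2. Where stored pre-IN tissue happens to exist, use it for the modifier analysis. State how many patients per arm have it and how they differ from the rest. If the tissue was taken before randomisation, the arms remain comparable within that subset, though it may not represent all patients.
3. Otherwise, report the ASS1 result as an exploratory association with expression measured after the IN period, and not as a pre-treatment factor that alters IN efficacy.

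The cost is a few sentences and one additional between-arm table. No new visit or sample is required. The downside is a narrower ASS1 claim where no earlier tissue is available.
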